### Participants and outcomes

This study will include two main groups of participants: (1) individuals with one or more NCDs who receive care from PHC services and (2) healthcare professionals working in these settings who provide care to such individuals. The eligibility criteria for each group, as they relate to MARES-1, MARES-2 and MARES-3 are detailed in table 1. The primary outcome for each objective, along with the instruments and measures used for their assessment, is presented in table 2.

**Table 1 T1:** Eligibility criteria

Inclusion criteria	Exclusion criteria
MARES-1 and MARES-2	
Individuals	
Attending PHC services Diagnosed with one or more NCDs Aged ≥30 years	Clinically unstable in the past month (worsening symptoms requiring emergency care or hospitalisation) Currently pregnant Active pulmonary tuberculosis or undergoing treatment for pulmonary tuberculosis Acute respiratory infection Cognitive impairment that prevents understanding of the COLA-6 questionnaire, that is, MMSE score ≤20^48^ Contraindications to spirometry or inability to perform the test Declining to participate in the study

MARES-2	
Healthcare professional	
Providing care to individuals with NCDs attending PHC services Includes physicians, nurses, physiotherapists and community agents	Did not complete training to apply the COLA-6 questionnaire Declining to participate in the study

MARES-3	
Individuals	
The inclusion and exclusion criteria will be the same as those for individuals of MARES-1 and MARES-2, considering that this is a follow-up from these previous studies.	
Participants will be included in the follow-up phase if they meet either of the following criteria: Identified as having abnormal spirometry or diagnosis of CRD in MARES-1 Identified as being at high risk for CRD through the COLA-6 questionnaire in MARES-2	Participants will be excluded from the follow-up phase if: Clinically unstable in the past month (worsening symptoms requiring emergency care or hospitalisation) Currently pregnant Diagnosed with active pulmonary tuberculosis or undergoing treatment for pulmonary tuberculosis Presenting with an acute respiratory infection Having contraindications to spirometry or inability to perform the test Declining to participate in the study

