#### MARES-1

Data collection will be conducted at a single visit by a member of the UFSCar research team. All eligible participants will provide written informed consent prior to study procedures. The following procedures will be carried out:

Initial assessment (details below).Application of case-finding tools questionnaires:COLA-6 questionnaire.^19 20^Symptom-Based questionnaire (SBQ).^32^Fractional exhaled nitric oxide (FeNO) measurement.Spirometry (prebronchodilator and postbronchodilator).Application of disease-specific questionnaires:Chronic Airways Assessment Test (CAAT) for all individuals with abnormal spirometry or CRD.^33 34^Asthma Control Questionnaire (ACQ-7) for individuals with isolated or overlapping asthma.^35 36^Participants identified with abnormal spirometry results and diagnosis of CRD will be provided with an informational leaflet containing basic guidance about abnormal spirometry or asthma or COPD and how to access diagnostic and treatment services for respiratory conditions.

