### Assessments

All assessments will be conducted by a team of clinical researchers who were previously trained to ensure the accuracy and consistency of data collection.

MARES-1 initial assessment: The research team will collect information about medical history, CRD risk factors, history of infections, current medications and previous hospitalisations. Additional information on childhood growth and development, socioeconomic profile and anthropometric data will be gathered.

COLA-6 questionnaire: The COLA-6 questionnaire,^19^ translated and culturally adapted into Portuguese^20^ (see online supplemental material), will be administered (MARES-1 and MARES-2). The questionnaire comprises three sections: (1) six questions addressing respiratory symptoms, functional status and exposure to risk factors; (2) one question on age and (3) one question involving peak expiratory flow (PEF) measurement. Scoring assigns 1 point for each affirmative response to the six questions, 1 point if participant is aged ≥55 years, 1 point if PEF is between 250–399 L/min, and 2 points if PEF is <250 L/min, resulting in a total score ranging from 0 to 9 points. PEF will be measured using a Mini-Wright Standard Peak Flow Meter (Clement Clarke, Essex, England). Participants will perform three forced exhalations from full lung capacity, using a nose clip, and following proper technique (avoiding neck flexion and tongue obstruction of the mouthpiece). Standardised verbal encouragement will be provided, with a 30 s pause between manoeuvres. If the two highest values differ by more than 40 L/min, up to two additional manoeuvres will be performed, to a maximum of five attempts. The highest recorded PEF value will be used.^37^ A COLA-6 score ≥4 is considered a positive test, representing the optimal combination of sensitivity and specificity for predicting the risk of COPD.^19^ Participants identified as at risk of CRDs in MARES-2 will receive their results along with educational material developed with the support from our patient and public involvement (PPI) group. The materials provide information on CRDs, risk factors, symptoms, diagnosis and treatment.

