SBQ: The SBQ questionnaire^32^ will be administered to compare performance with COLA-6 (MARES-1). The SBQ consists of 11 questions covering age, smoking history, body mass index, cough, wheezing, allergies, dyspnoea, exposure to dust or chemical particles and the presence of respiratory diseases during childhood. A total score of ≥17 indicates a higher risk for COPD.^32^

FeNO measurement: FeNO will be measured using a portable analyser (FeNObreathe, Geratherm Medical Latin America, Brazil), following American Thoracic Society guidelines^38^ to assess type 2 airway inflammation (MARES-1 and MARES-3). Subjects will be seated comfortably and instructed to inhale through the mouthpiece for 2–3 s to total lung capacity, followed by a steady exhalation lasting at least 6 s, without air leakage. An expiratory flow rate of 50 mL/s will be maintained, monitored by a sound signal. Up to six manoeuvres will be allowed, with 30 s intervals between attempts. The highest value among three acceptable measurements will be used, ensuring quality control by limiting deviation to ≤2.5 ppb or 10% within 15 min. FeNO levels will be classified as low/normal (<25 ppb), intermediate (25–50 ppb) or high (>50 ppb).^39^

Spirometry: Lung function will be assessed using a portable spirometer (Spirobank II Advanced, MIR, USA) to confirm or exclude CRDs (MARES-1 and MARES-3). Testing will follow American Thoracic Society and European Respiratory Society standards, ensuring A or B quality grades. ^40 41^At least three forced, acceptable and reproducible manoeuvres will be performed before and 20 min after inhalation of 400 mcg of salbutamol sulfate. Spirometry results will be reviewed and interpreted by a board-certified pulmonologist.

Participants will be classified based on spirometry and FeNO results (figure 2) into two groups, primarily according to the recommendations of the Global Initiative for Chronic Obstructive Lung Disease^42^ and the Global Initiative for Asthma.^27^

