### Data analysis

MARES-1: We will summarise the demographic and clinical characteristics of participants overall. Based on spirometry results, we will report the prevalence of COPD, asthma, PRISm and restriction, alone and in combination, with 95% CIs. For the primary analysis, we will calculate the AUC of the ROC curves for COLA-6 compared with the gold standard spirometry diagnosis separately for combined CRDs, asthma, COPD, PRISm and restriction. Using the previously published threshold for COLA-6 scores of ≥4,^19^ we will also calculate sensitivity, specificity, and negative and positive predictive values. In addition, based on the ROC curve, we will identify the COLA-6 score threshold that achieves sensitivity of at least 90%. Similar AUC analyses will be conducted for SBQ and results compared with those for COLA-6.

MARES-2: Descriptive statistics will be used to characterise the patient and healthcare professional demographics. Quantitative analysis will assess fidelity data, with categorical variables reported as frequencies (percentages). The qualitative analysis of the interviews will follow Braun and Clarke,^46^ which consists of six phases: (1) familiarisation with the data set; (2) coding; (3) generation of initial themes; (4) development and review of themes; (5) refinement, definition and naming of themes and (6) writing. The initial analysis of the transcripts obtained from the interviews will be carried out using the Web Qualitative Data Analysis software (University of Aveiro, Aveiro, Portugal) and completed manually using a Microsoft Excel spreadsheet. To ensure reliability, the criteria of credibility, transferability, dependability and confirmability will be used.^47^

MARES-3: Descriptive statistics will be used to describe the individual samples from MARES-1 and MARES-2. For patients from MARES-2, the proportions diagnosed with CRDs at spirometry will be calculated. For individuals in MARES-1, who have longitudinal data, the mean change in spirometric values from baseline to 6 months will be summarised and the proportion with improved values will be reported. Additionally, baseline and 6-month CAAT and ACQ-7 questionnaire scores, and FeNO will be summarised and mean changes reported. Estimates will be provided with 95% CIs. The qualitative analysis of the interviews will follow Braun and Clarke,^46^ as described above for MARES-2.

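### MARES-1 excludes people who cannot perform spirometry, often after COLA-6 is scored: specificity is likely overstated, and other accuracy measures may be biased either way

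*Protocol article*

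**What the plan says.** The MARES-1 objective is the discriminative accuracy of COLA-6 in people attending primary healthcare (PHC) services for non-communicable diseases (NCDs).

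- **Eligibility (Participants and outcomes, Table 1).** Exclusions for individuals in MARES-1 and MARES-2 include "Contraindications to spirometry or inability to perform the test".
- **Visit (MARES-1, data collection).** "Data collection will be conducted at a single visit by a member of the UFSCar research team". After the initial assessment the list gives "Application of case-finding tools questionnaires:COLA-6 questionnaire", then the comparator questionnaire (SBQ), and then "Fractional exhaled nitric oxide (FeNO) measurement.Spirometry (prebronchodilator and postbronchodilator".
- **Index test (Assessments, COLA-6).** The score runs from 0 to 9 and is positive at 4 or more. PEF can supply one point, or "2 points if PEF is <250 L/min".
- **Reference test (Assessments, Spirometry).** Testing follows the cited standards, "ensuring A or B quality grades".
- **Analysis (Data analysis, MARES-1).** "we will calculate the AUC of the ROC curves for COLA-6 compared with the gold standard spirometry diagnosis". Sensitivity, specificity and both predictive values follow at the threshold of 4, together with a search for a threshold reaching at least 90% sensitivity. Table 2 adds accuracy with and without PEF.

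**The concern.** Eligibility for an accuracy study should not turn on how the reference test works out once the index test has been scored. A contraindication can be screened beforehand. Failure to produce acceptable, repeatable blows is normally seen only when the person tries, and in the listed order COLA-6 is then already on record.

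The loss is unlikely to be random with respect to the score. A weak or poorly coordinated forced exhalation can lower PEF, which adds COLA-6 points, and can also make spirometry unusable. In routine use the tool would still flag such a person.

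What would then be estimated is accuracy among people able to produce usable spirometry, not among PHC attenders with NCDs. The difference matters because the Introduction justifies the tool by the scarcity of spirometry. The 90%-sensitivity threshold and the comparison with and without PEF would come from the same selected group. The analysis without PEF removes the points but does not bring back the people.

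**Working it through.** **Inputs from the protocol (Sample size, MARES-1):** N = 859, COPD prevalence 17%, sensitivity 45.7%, specificity 86.5%.

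**The plan's own figures.** 0.17 × 859 = 146 COPD cases, as stated, leaving 713 non-cases. The stated AUC half-width of 4.5% falls within the 4.2% to 5.2% given by common variance formulas. The article does not name its formula, and nothing below depends on this.

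**Analysed group, everyone with usable spirometry:**
- true positives 146.03 × 0.457 = 66.7; false negatives 79.3
- false positives 712.97 × 0.135 = 96.3; true negatives 616.7
- PPV = 66.7 / (66.7 + 96.3) = 40.9%

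**Assumptions (none is in the document).** A share *f* of all those scored fails spirometry, so M = 859·f/(1−f) people are missing; at f = 10%, M = 95.4. Two accuracy patterns are tried in the missing group: A (specificity 70%, sensitivity 60%) and B (specificity 50%, sensitivity 70%). Their COPD share is set at 8.5%, 17% or 60%.

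**Worked case: f = 10%, COPD share 17%, pattern A.** The missing comprise 16.2 diseased and 79.2 disease-free.
- Specificity = (616.7 + 0.70 × 79.2) / (713.0 + 79.2) = 672.2 / 792.2 = 84.9%
- Sensitivity = (66.7 + 0.60 × 16.2) / (146.0 + 16.2) = 47.1%
- PPV = 76.5 / (76.5 + 120.0) = 38.9%

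**All cases at f = 10%.** The last column is the one-threshold area, (sensitivity + specificity)/2.

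| COPD share in missing | Pattern | Specificity | Sensitivity | PPV | One-threshold area |
|---|---|---|---|---|---|
| analysed group only | – | 86.5% | 45.7% | 40.9% | 0.661 |
| 8.5% | A | 84.7% | 46.5% | 36.9% | 0.656 |
| 8.5% | B | 82.5% | 47.0% | 34.1% | 0.648 |
| 17% | A | 84.9% | 47.1% | 38.9% | 0.660 |
| 17% | B | 82.9% | 48.1% | 36.5% | 0.655 |
| 60% | A | 85.7% | 49.7% | 48.4% | 0.677 |
| 60% | B | 84.6% | 52.6% | 48.1% | 0.686 |

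With the COPD share at 17%, moving *f* from 5% to 15% takes specificity from 85.7% (pattern A, 5%) to 81.0% (pattern B, 15%).

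**Direction.**
- Specificity is overstated whenever disease-free people who fail are COLA-6 positive more often than 13.5%.
- Sensitivity is understated if diseased people who fail are positive more often than 45.7%, and overstated if less often.
- PPV is overstated only while the PPV among the missing is below 40.9%. The break-even disease odds are (0.409/0.591) × (1 − specificity)/sensitivity in the missing group. This gives a COPD share of 26% (A) or 33% (B). For any chronic respiratory disease (309 abnormal, 550 normal, same sensitivity and specificity assumed), the analysed PPV is 65.5% and the break-even shares are 49% and 58%.
- The one-threshold area falls or rises with the disease share of the missing, so the AUC bias has no fixed sign.

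**The case against.** **Timing is inferred.** Table 1 sets inability beside criteria that can be checked in advance, the MARES-1 section speaks of eligible participants consenting before procedures, and the listed order is not declared fixed. This stands to the extent that inability is not always found after scoring. It does not remove the point: ability to reach an acceptable grade is largely shown by attempting the test, and the article describes no attempt before COLA-6.

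**The A/B grade is a conduct standard.** No sentence drops people graded below B, and handling of missing reference results is commonly left to the analysis plan. Both statements are fair, and silence on missing data is not the finding. The finding is the eligibility rule that Table 1 does state.

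**The PEF route is limited.** PEF gives at most 2 of the 4 points needed, so at least two must come from elsewhere. Standardised encouragement, up to five attempts and use of the highest value also reduce technique error. These features reduce the effect without abolishing it.

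**Stronger readings.** A reader might infer that PPV and AUC are inflated too. The document does not support this: if people fail because they are ill, true positives are lost and PPV is understated. A reader might also infer a large effect by adding one or two points to the full score of everyone who fails. That counts PEF twice, since those points already sit within the 0 to 9 score. Nor has it been shown that the exclusion favours the version with PEF.

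**Conclusion.** The point holds in limited form. Table 1 states an exclusion that depends on the reference test, and the listed visit order means that much of it would act after COLA-6 is scored. It is plausibly related to the score through the shared forced exhalation, and it narrows the population in the objective.

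Upward bias in specificity is the likely direction: about 0.8 to 4.0 percentage points if 10% fail, under the assumed patterns. PPV could move from 40.9% to anywhere between 34.1% and 48.4% in the same cases, so no direction should be claimed for it, nor for sensitivity or AUC. The failure rate, the disease share and the COLA-6 positivity of those who fail are all assumptions. An uncertain direction is itself a reason to keep these people visible. The change should be made, and it is best made before enrolment ends, because data on people logged as ineligible may not be retained.

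**What to change.** **Table 1.** Limit the MARES-1 exclusion to contraindications or inability known before COLA-6 is given. Anyone scored on COLA-6 without usable spirometry stays in MARES-1 as *reference result indeterminate*.

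**Data analysis, MARES-1.** Beside the analysis of those with usable spirometry:
1. Report the number indeterminate, their COLA-6 positivity and their PEF points.
2. Give sensitivity, specificity, PPV and NPV with the indeterminate group counted all as diseased and all as disease-free. These two allocations give the limits for PPV and NPV. For sensitivity and specificity, add the two mixed allocations (positives diseased with negatives disease-free, and the reverse), because all-or-none counting does not span the range. In the worked case above (33.5 positive and 61.9 negative among the missing), it gives sensitivity of 41.5% and 45.7%, while the value built into that case is 47.1%. The mixed allocations give 32.1% and 55.8%.
3. Treat multiple imputation as supplementary only, with its missing-at-random limit stated. A model fitted in people with usable spirometry reads low PEF as a sign of disease, which does not suit people whose low PEF reflects technique.

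**Cost.** One wording change in Table 1 and a few lines of analysis and reporting, with no new visit or procedure. Specificity may look less favourable, and the bounds will be wide if many fail.

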### Recruitment

For MARES-1, individuals will be recruited from PHC services, including BHUs and FHUs, located in the municipalities of São Carlos and São Paulo, Brazil. Eligible individuals with NCDs will be recruited through three primary strategies: (1) individuals receiving routine care for established NCDs at BHUs/FHUs, such as scheduled consultations for hypertension or diabetes; (2) individuals with NCDs identified through proactive outreach by community health agents and (3) individuals from BHUs/FHUs with NCDs who become aware of the study via passive recruitment strategies, including informational posters, communication from healthcare staff, peer referrals or invitations extended during service delivery days. Recruitment materials, including posters with contact details for the research team, will be displayed in BHUs/FHUs, and direct invitations will be issued during routine service encounters. All recruitment procedures will be conducted in accordance with ethical principles, ensuring the protection of participants’ rights to privacy and autonomy.

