### Objective

*Multimorbidity Approach for*
*REspiratory Solutions (MARES-1)*: To evaluate the discriminative accuracy of the COLA-6 questionnaire in identifying Brazilian individuals with CRDs who attend PHC services for the management of other NCDs.

*MARES-2*: To assess the feasibility of implementing the COLA-6 questionnaire in PHC settings for NCD care in Brazil by the PHC professionals.

*MARES-3*: To investigate how individuals with NCDs attending PHC services, identified as having abnormal spirometry, CRD or high risk for CRDs, access further diagnostic and treatment services in Brazil.

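### MARES-1 reports prevalence, PPV and NPV from a mixed convenience sample that includes self-presenting volunteers, with no stated handling of recruitment route

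*Protocol article*

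**What the plan says.** **Target.** The MARES-1 objective (Objective section) is the accuracy of COLA-6 in "identifying Brazilian individuals with CRDs who attend PHC services for the management of other NCDs". The Introduction places the intended use in routine NCD care, which is where professionals apply the tool in MARES-2.

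**Eligibility.** Table 1 applies to every participant, however recruited: "Attending PHC services Diagnosed with one or more NCDs Aged ≥30 years". It does not exclude people with chronic respiratory symptoms or an already known CRD.

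**Recruitment.** The Recruitment section lists three strategies:
1. Routine care: "individuals receiving routine care for established NCDs at BHUs/FHUs, such as scheduled consultations for hypertension or diabetes".
2. Outreach: community health agents actively seek out patients who have an NCD.
3. A passive strategy, still confined to patients of the units who have an NCD: those who "become aware of the study via passive recruitment strategies, including informational posters, communication from healthcare staff, peer referrals". Service-day invitations also fall under it.

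No consecutive or random sampling is described, and no quota or cap by strategy.

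**Analysis.** Under Data analysis, "we will report the prevalence of COPD, asthma, PRISm and restriction, alone and in combination, with 95% CIs". The AUC is the primary analysis. Sensitivity, specificity, PPV and NPV follow at a score of 4 or more, and a further threshold is chosen to reach at least 90% sensitivity. No split or adjustment by recruitment strategy is stated.

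**Sample size.** The plan assumes COPD prevalence of 17%, sensitivity 45.7% and specificity 86.5%, with N=859. If prevalence is lower than expected, more people will be case-found until the target counts are met. Nothing says which strategy supplies them.

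**The concern.** Someone who responds to a poster or a friend's suggestion may do so because they cough, wheeze or suspect a lung problem. If so, the volunteer part of the sample has a different CRD prevalence and symptom profile from patients met during ordinary NCD visits.

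Prevalence, PPV and NPV depend directly on case mix. A 95% CI around a pooled prevalence conveys sampling error only; it does not cover error from how people entered the sample. Spectrum effects are also possible, because COLA-6 gives points for respiratory symptoms, functional status and exposures. Selection on symptoms therefore acts on the index test itself and could change sensitivity, specificity and the 90%-sensitivity threshold.

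The readers most affected are those who would carry the predictive values or the new threshold into routine NCD clinics. The rule for extending recruitment adds to this, since the mix of strategies may drift as targets are pursued. The stated limitations cover generalisability beyond Brazilian PHC, but not volunteer selection.

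**Working it through.** **Inputs from the protocol article (Sample size).** N = 859; COPD prevalence p = 0.17; sensitivity Se = 0.457; specificity Sp = 0.865; expected counts 146 COPD, 77 asthma, 86 PRISm or restriction, 309 abnormal, 550 normal.

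**Step 1: reproduce the plan's case mix.** 0.17 × 859 = 146.03; 146 + 77 + 86 = 309; 859 − 309 = 550. All agree.

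**Step 2: sampling error of the prevalence.** Half-width = 1.96 × √(0.17 × 0.83 / 859) = 0.0251, about 2.5 points.

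**Step 3: predictive values with no volunteer effect.**
- PPV = p·Se / [p·Se + (1−p)(1−Sp)] = 0.07769 / (0.07769 + 0.11205) = 40.9%.
- NPV = (1−p)·Sp / [(1−p)·Sp + p(1−Se)] = 0.71795 / (0.71795 + 0.09231) = 88.6%.

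**Step 4: shift from volunteers.** Let s be the volunteer share and r the ratio of volunteer prevalence to that of the other participants. The document gives neither, so both are assumptions. Pooled prevalence = 0.17 × [(1−s) + s·r], so the shift is 0.17 × s × (r−1). It exceeds the half-width when s × (r−1) > 0.0251 / 0.17, about 0.15.

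With Se and Sp held fixed:

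| s | r | Pooled prevalence | PPV | NPV |
|---|---|---|---|---|
| none | – | 17.0% | 40.9% | 88.6% |
| 10% | 1.25 | 17.4% | 41.7% | 88.3% |
| 25% | 1.5 | 19.1% | 44.5% | 87.1% |
| one third | 1.5 | 19.8% | 45.6% | 86.6% |
| 50% | 2 | 25.5% | 53.7% | 82.3% |

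For the one-third row the shift is 0.17 × (1/3) × 0.5 = 0.0283, or 2.8 points, slightly more than the half-width. A ratio below 1 would move prevalence the other way.

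**Step 5: is the direction of the PPV error known?** Selection on symptoms would plausibly raise sensitivity and lower specificity, so holding both fixed is not neutral. Keep the one-third example (p = 0.1983) but assume pooled Se = 55% and Sp = 80%. PPV = 0.1091 / (0.1091 + 0.1603) = 40.5%, almost the 40.9% of Step 3. The prevalence effect and the specificity effect on PPV can cancel.

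**The case against.** The strongest reply is that everyone recruited belongs to the population in the objective. Table 1 requires PHC attendance and a diagnosed NCD, and strategy 3 is itself limited to people from the units with NCDs. Strategy 2 is active outreach by community health agents, who are among the professionals applying COLA-6 in MARES-2. Strategy 3 includes direct invitations as well as posters. All of this stands. A reader might infer that the sample is drawn from the wrong population, or that only strategy 1 represents the objective. The document supports neither: scheduled consultations are given there only as an example.

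A reader might also infer that PPV will be inflated. That is not established. Poster wording is not shown, the shares and prevalences are assumed, and Step 5 shows the effects can offset each other.

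Third, the primary AUC does not depend directly on prevalence, and Table 2 lists AUC, sensitivity and specificity but not prevalence or predictive values. This is right and limits the seriousness of the point, although spectrum effects can still reach accuracy measures.

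Finally, a condensed article may omit a CRF field or a stratified table that exists in the full protocol or SAP. That is possible, and if the route is already recorded, only the reporting remains to be settled. But the mix of recruitment routes and the prevalence reporting are stated in the article, and a route not captured at enrolment may not be recoverable later.

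**Conclusion.** The point holds as one about sampling within the eligible population. MARES-1 will report prevalence, PPV and NPV from a mixed convenience sample that includes volunteers, and the article states no handling of recruitment route.

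The possible error is material but not determinable. Over assumed volunteer shares of 10% to 50% and prevalence ratios of 1.25 to 2, pooled COPD prevalence would be 17.4% to 25.5% instead of 17%. The lower end lies well inside the 2.5-point half-width and the upper end well outside it. The corresponding PPV range of 41.7% to 53.7% rests further on fixed sensitivity and specificity, which symptom-based selection would probably disturb. These figures show what is possible; they do not predict the outcome.

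The planned N and the use of the pooled sample for the primary AUC need not change.

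**What to change.** - Record the recruitment route for each MARES-1 participant at enrolment. Within strategy 3, separate people who present themselves (posters, peer referral) from those invited by staff during care or outreach.
- Keep the pooled sample for the primary AUC.
- Report prevalence, PPV, NPV, sensitivity and specificity by route, and add a sensitivity analysis that excludes self-presenting volunteers. No single route need be made the primary estimate.
- State volunteer selection as a limitation.

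**Cost.** One CRF field and one table, with wider intervals within each route. If one third (about 286 people) were self-presenting, the prevalence half-width at 17% would be 1.96 × √(0.1411 / 286) = 4.4 points in that group. In the remaining 573 it would be 1.96 × √(0.1411 / 573) = 3.1 points. Sensitivity by route would be much less precise: about 49 COPD cases among 286 people gives 1.96 × √(0.457 × 0.543 / 49), or 14 points. The route-specific accuracy figures should therefore be read as descriptive.
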